### Recruitment {15}

Formal invitations will be sent out by the ANDA Secretariat to the site leads/representatives of eligible sites to provide an explanatory statement of the research, a Participant Information and Consent Form (PICF) detailing the exact nature of the study; what it will involve for the participating centre; the implications and constraints of the protocol; and any risks involved in taking part and contact details for the project lead.

### Who will take informed consent? {26a}

Participation in this research is completely voluntary and there are no consequences for those centres who choose not to participate. Sites who wish to participate in this research will notify the project lead of their intent to participate and consent through the return of a signed PICF via email to the ANDA Secretariat or the project lead. The project lead will countersign and return the PICF to participating centres. Details and documentation of participating sites will be maintained by the ANDA Secretariat to maintain the coded nature of enrolment (i.e. the project lead will know the names of individual staff participating, but not the unique ANDA identifying number for the centre they work for).

Sites will be asked to respond within 7 days, after which time a reminder email will be sent. Subsequent reminders will be sent up to the time of the end of the 6-week recruitment period.

### Additional consent provisions for collection and use of participant data and biological specimens {26b}

No biological specimens will be collected as part of this trial or sub-study. The additional consent provisions for collection and use of (non-patient) data in an associated sub-study to validate the survey instrument are detailed in the section ‘Reliability and validity of survey instrument (sub-study)’.

## Interventions

### Explanation for the choice of comparators {6b}

ANDA data has shown room for improvement in key processes and clinical outcomes over the previous 8 years; hence, there is an urgent need for reformatting the feedback. Our formative work with ANDA centres identified desired changes to data presentation in ANDA feedback. The comparator will hence be ANDA feedback only, but this feedback will be redesigned to meet these identified needs.

### Intervention description {11a}

#### Interventions

##### Feedback report

Both the intervention and control groups will receive the redesigned ANDA feedback report. This feedback report will be informed by the formative qualitative study [16] and developed by the lead author in consultation with the investigator group, including clinicians and an audit and feedback expert. The draft design of the report will then be modified based on their advice about clarity and feasibility, in a co-design process. The redesigned feedback will be configured for an automatic generation process by the ANDA data management team and will be delivered electronically to the contact person for each participating diabetes centre as a PDF document at one timepoint (December 2021).

##### PowerPoint slide deck

A partially pre-populated PowerPoint slide deck template to facilitate presentation of data within clinical practice teams will also be provided with the feedback report. The slide deck will be developed by the project lead in consultation with the ANDA-EFFECT investigator group and will allow diabetes centres to enter the data from their ANDA feedback report into the PowerPoint template.

#### Control arm

Standard treatment/care: Participating diabetes centres randomised to the control arm will only receive the feedback report and PowerPoint slide deck, as above.

#### Intervention arm

In addition to the feedback report and PowerPoint slide deck, participating diabetes centres randomised to the intervention arm will receive a tailored theory-based intervention designed to address identified, modifiable barriers to utilising and implementing the recommendations from ANDA feedback. The design of the intervention is underpinned by a formal qualitative study to elicit current quality improvement practices and barriers to implementation of feedback [16].

##### Intervention components

The intervention comprises a package of educational resources and community of practice forums, delivered on the NADC website. These resources will include:A 45-min QI webinar will be developed to guide participants, including short instructional videos to guide participants through understanding their data, along with presentations delivered by external QI expertsAudio-visual stories from clinical change champions from a range of metropolitan and regional services in different states in Australia, identified through prior NADC involvement. These stories will describe how change champions have used ANDA data to facilitate QI activitiesPeer-led community of practice forums will be provided on the NADC website to facilitate participants to share knowledge and ideas related to the effective use of ANDA data. These forums will be moderated by the project lead

These resources will be produced by the project lead and the investigator group in collaboration with the NADC to maximise their clinical outreach. To prevent contamination between study groups, the intervention resources will be password-protected to only be available to intervention sites.

##### Delivery

The intervention resources will be made available to participants in the intervention arm by the ANDA research team approximately 3 months before they receive their redesigned ANDA audit feedback, to allow time for familiarisation with the resources. These resources will remain accessible to participants in the intervention arm following the delivery of ANDA audit feedback. There are no a priori plans for centre-specific tailoring or modification of the intervention resources. An overview of the trial arms is shown in Fig. 1.

**Fig. 1 Fig1:**
[figure not shown]
Overview of ANDA-EFFECT trial arms

#### Expectation of engagement

The expectation of participating centres will be made clear in the explanatory recruitment statement. Centres participating in the intervention arm will be expected to complete a minimum of three activities from the intervention resources, including:Attendance at the QI webinar—this will be hosted initially in the evening, followed by a live question and answer session. The webinar will be replayed with a live question and answer session during a lunch hour, to facilitate maximum uptakeViewing of at least one ‘clinical change champion’ videoParticipation in at least one peer-led forum

We anticipate that these activities will take up to 80 min in total, which could be comprised of multiple 5–10-min viewing blocks.

### Criteria for discontinuing or modifying allocated interventions {11b}

There are no criteria for discontinuing or modifying the allocated interventions, as the interventions are delivered to participating diabetes centres, not individual patients.

### Strategies to improve adherence to interventions {11c}

The trial will be promoted by the clinical partners (NADC) to their members who have participated in ANDA in 2021. A potential limitation of the recruitment strategy is that this is a pragmatic trial utilising an existing audit and feedback activity, where participation in ANDA 2021 has been impacted by the effects of COVID-19 on clinical practice [18]. As such, there is a lower than usual number of eligible diabetes centres from which to recruit, and the ANDA-EFFECT investigator group acknowledge that it may be difficult to reach optimal sample size; however, all efforts will be made to maximise participation.

#### Intervention fidelity

The interventions will be delivered in a standard, pre-recorded manner to all participants and as such are not susceptible to fidelity delivery variability in the way that educational interventions delivered as live sessions can be [19]. Our fidelity evaluation will therefore focus on whether participants engage with the interventions, as detailed in the section ‘Methods in analysis to handle protocol non-adherence and any statistical methods to handle missing data {20c}’.

### Relevant concomitant care permitted or prohibited during the trial {11d}

This is a cluster randomised trial targeting clinical practices, not patients. As such, there are no restrictions on concomitant care.

### Provisions for post-trial care {30}

Not applicable as this trial is testing interventions aimed at the cluster (practice) level rather than the patient level. As such, patient care is independent of the trial and will be administered as per normal processes by participating diabetes centres.

### Outcomes {12}, including plans for assessment and collection of outcomes {18a}

#### Primary outcomes

To address the aim of the trial to assess the impact of the interventions on clinical outcomes, we will collect data on HbA1c levels of patients attending participating centres for care. To address the aim of the trial regarding practitioner perceptions, we will collect data related to the acceptability and utility of the interventions.

##### HbA1c at 6 months

HbA1c is routinely collected for patients from participating diabetes centres as part of ANDA. Baseline de-identified (coded) mean HbA1c percentage will be extracted for each participating diabetes centre from routine ANDA data collection in 2021. Follow-up data will be collected as part of the ANDA 2022 audit (6 months after delivery of the 2021 ANDA site reports).

##### Acceptability and utility of the intervention at 3 months

To assess how well the interventions address the issues raised in our formative work [16] at a practitioner level, the acceptability and utility of the intervention will be assessed via a 15-min online survey, which we will design specifically for this purpose. This survey will adapt on a survey (ENACT) used by a group of audit and feedback researchers with permission from the authors (personal communication) to assess the acceptability of online audit and feedback interventions [20]. The ENACT survey will be adapted to allow inclusion of parts of an existing ANDA questionnaire. Surveys will be completed 3 months after the delivery of site reports (feedback). Participants will rate a variety of factors about the feedback using Likert scales and open-ended text comments. The developed, combined survey will be validated for test/retest reliability and face validity prior to its use in outcome assessment (see sub-study below). The survey will be delivered to participants as an email link sent to the registered contact persons for the participating sites and will be conducted through REDCap [21], a secure web application for online survey and database management hosted at Monash University. The survey will be delivered 3 months after the delivery of the ANDA feedback reports.

#### Secondary outcomes

##### Other clinical and process of care outcomes

Other de-identified (coded) baseline clinical and process of care outcomes will be extracted from routine ANDA data collection in 2021, using the ANDA data collection form. These will include mean systolic blood pressure (mm Hg) and associated prescribing rates of hypertensives as well as mean total cholesterol, low-density lipoprotein (LDL) and high-density lipoprotein (HDL) (mmol/L) and the associated prescribing rates of lipid-lowering medications. In the same manner as the primary clinical outcome, follow-up data will be collected as part of the ANDA 2022 audit (6 months after the delivery of the 2021 ANDA site reports). All clinical measures included in the standard ANDA data collection form are collected independently of this trial, either by the participating diabetes centres or by the independent pathology services undertaking clinical testing for the participating centres as part of their routine care. As these results are submitted to ANDA in a coded (de-identified) manner, managed by the ANDA data management team and reported in aggregate, the ANDA-EFFECT investigator group do not have access to individual patient data for these variables and will extract mean clinical outcomes from the existing ANDA data set.

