**Methods:**

Two-armed cluster randomised trial with Australian Diabetes Centres that participated in the Australian National Diabetes Audit in 2021 as the clusters, stratified by location and type of centre. We aim to recruit 35 diabetes centres in each arm. Both the intervention and control arms will receive an augmented feedback report, accompanied by a partially pre-populated slide deck. In addition, the intervention arm will receive a tailored theory-based intervention designed to address identified, modifiable barriers to utilising and implementing the recommendations from diabetes audit feedback. The co-primary outcomes are (1) HbA1c at the patient level, measured at 6 months after delivery of the intervention, and (2) the acceptability and utility of the augmented feedback and cointerventions at the practitioner level, measured at 3 months after delivery of the intervention.

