The Australian National Diabetes Audit (ANDA) is a longstanding clinical audit and feedback activity which has been administered by Monash University and the National Association of Diabetes Centres (NADC) since 2013. This clinical audit routinely collects de-identified information about clinical markers (e.g. HbA1c, blood pressure and lipid levels) and process of care measures (e.g. proportion of patients receiving annual retinal examination) among people living with diabetes in Australia who attend health services based in primary care, secondary or community care and tertiary referral centres. During a 4-week period in May through to July of each year, data is collected for all consecutive patients attending participating diabetes centres, using a standardised data collection form (Additional file 1). Data is collated and analysed, and participating centres then receive feedback in the form of an individualised benchmarking report which is made available to centres in an electronic format. Currently, the individualised report is approximately 200 pages long and provides detailed information on clinical performance in terms of clinical and process measures. Each measure is benchmarked to the mean achieved across all participating centres. Clinical performance indicators are presented in the form of tables and bar charts, allowing individual centres to interpret their data and undertake quality improvement activities as they see appropriate. While these individualised reports are only released to the individual diabetes centre, the de-identified data across all centres is also collated into a national report that is publicly available [9].

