## Statistical methods

### Statistical methods for primary and secondary outcomes {20a}

#### Primary outcomes

Differences between the experimental and control groups will be analysed by the intention-to-treat approach. For the first co-primary outcome of difference in HbA1c, we will use the linear mixed effects model to compare the between-group difference in mean HbA1c at 6 months after delivery of the intervention while adjusting for clustering of patients with site by including a centre random intercept. Appropriate transformations of the data will be undertaken in the event of departure from normality. Only if the first co-primary outcome is statistically significant at a two-sided level of significance of <0.05, we will test the second co-primary of acceptability and utility of interventions for superiority using the chi-squared or Fisher’s exact test as appropriate. This will preserve the overall type 1 error at <0.05.

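### The protocol contradicts itself on whether patient records or only centre means will be available for the HbA1c and secondary clinical analyses

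*Protocol article*

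**What the plan says.** **Text that needs patient records.** The Abstract (Methods) defines the first co-primary outcome as "HbA1c at the patient level, measured at 6 months after delivery of the intervention". Statistical methods {20a}, Primary outcomes, compares mean HbA1c at 6 months in a linear mixed model, "adjusting for clustering of patients with site by including a centre random intercept", and allows transformation if normality fails. The Secondary outcomes paragraph that follows applies the same type of model to the other clinical endpoints. Sample size {14} counts 3500 patients and uses a standard deviation of 2.3 and an intracluster correlation of 0.070. Under Eligibility criteria {10}, the Patient data paragraph says that coded patient data on set fields will be extracted from ANDA.

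**Text that points to centre means.** Other clinical and process of care outcomes says that the investigator group "do not have access to individual patient data for these variables and will extract mean clinical outcomes from the existing ANDA data set". The sentence before it is general: "All clinical measures included in the standard ANDA data collection form are collected independently of this trial". HbA1c is one of those measures, since Background {6a} lists "clinical markers (e.g. HbA1c, blood pressure and lipid levels" among what ANDA collects. For HbA1c itself, the section HbA1c at 6 months says that a baseline "mean HbA1c percentage will be extracted for each participating diabetes centre from routine ANDA data collection in 2021". For the outcome year it says only "Follow-up data will be collected as part of the ANDA 2022 audit", without giving the level.

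**The concern.** A random-intercept model separates variation between centres from variation between patients within a centre. It needs either several records per centre or summaries that carry the same information. One mean per centre carries neither the within-centre variance nor the centre size.

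If the analysts receive only means, the prespecified primary model has to be replaced once the data are in hand. The substitute would involve an open choice between unweighted, size-weighted and precision-weighted comparisons. With a coefficient of variation of cluster size of 0.730, these can give different estimates and have different power. A patient-level transformation of HbA1c would also be impossible from means of untransformed values. The same applies to the continuous secondary endpoints, where the conflict is explicit.

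**Working it through.** **Inputs, all from Sample size {14} unless noted.** Difference d = 0.5; SD = 2.3, so variance 5.29; ICC = 0.070; CV of cluster size = 0.730, so CV² = 0.5329; 35 centres per arm; 3500/70 = 50 patients per centre on average; alpha 0.05, two-sided per {20a}. Power below uses the noncentral t with 68 df; normal-approximation values are in brackets.

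**1. The protocol's own figure.**
- Equal clusters: design effect 1 + 49 × 0.07 = 4.43. SE = 2.3 × √(2 × 4.43/1750) = 0.164. Power 85% (86%).
- Mixed model with unequal clusters: L = 50 × 0.07/(50 × 0.07 + 0.93) = 0.790. Relative efficiency = 1 − 0.5329 × 0.790 × 0.210 = 0.912. Design effect 4.43/0.912 = 4.86. SE = 0.171. Power 82.0% (83.1%).

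The stated power of at least 80% is reproduced for the patient-level model. Recruitment also checks: 35/0.90 = 38.9, so 39 per arm and 78 in total.

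**2. What one mean per centre can identify.** With a single observation per centre and neither size nor SD, the variance of each observation is τ² + σ², and only that sum enters the likelihood. On 70 simulated centre means, the log-likelihood was −87.1447 for each of three splits of 0.64 between τ² and σ²: 0/0.64, 0.32/0.32 and 0.60/0.04. A test fit of the mixed model returned a Hessian that was not positive definite and an arbitrary equal split. What remains is an unweighted comparison of 35 against 35 means.

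**3. Power of the centre-level substitutes.** The protocol does not give the shape of the cluster-size distribution. Gamma and lognormal shapes with mean 50 and CV 0.73 are assumed to show a range.
- Unweighted: variance of a centre mean = 5.29 × (0.07 + 0.93 × E[1/m]).
  - Gamma: E[1/m] = 0.0428, variance 0.581, SE = √(2 × 0.581/35) = 0.182, power 77% (78%).
  - Lognormal: E[1/m] = 1.5329/50 = 0.0307, variance 0.521, SE 0.173, power 81% (83%).
- Weighted by centre size: design effect 1 + (1.5329 × 50 − 1) × 0.07 = 6.295, SE 0.195, power 71% (73%).
- Weighted by inverse variance, with weights 1/[5.29 × (0.07 + 0.93/m)]: SE 0.172 (gamma) or 0.170 (lognormal), power 82% or 83% (83% or 84%). This treats the variance components as known and needs each centre's size.

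**The case against.** A reader might infer that the primary model cannot be fitted at all. The documents do not support that, for four reasons.

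- The restriction is on the investigator group. The same sentence says that the ANDA data management team manages the results. Who will be blinded {17a} names a blinded analysis team, and {5d} lists the ANDA data manager separately from the investigators. Someone who holds the records could fit the model.
- The Patient data paragraph points to extraction of coded patient fields. Data management {19} gives the chief investigator, data manager and project lead access to the data.
- The no-access sentence sits under secondary outcomes. It reaches follow-up HbA1c only through the general sentence before it. The nearby phrase about the same manner as the primary outcome concerns when and where follow-up data are collected, not their level.
- HbA1c is described as a centre mean at baseline only. The {20a} model names no baseline covariate, so a baseline mean does not stop it being fitted.

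All four stand, but they do not remove the conflict. No section says that the data manager or analysis team will receive patient records and fit the model, and the access list in {19} does not name the biostatistician. The participant-level dataset in {31c} may mean practitioners, since the trial recruits no patients. Nor can this be left to an unseen analysis plan: the statements are printed and disagree.

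A second tempting reading is that the sample size is wrong. It is not shown to be. The 71% to 73% figure belongs to size weighting, which the protocol nowhere proposes, and the unweighted range straddles 80%.

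**Conclusion.** The contradiction is real. For the secondary clinical endpoints it is explicit: means only, yet a mixed model. For HbA1c it rests on a strong inference at follow-up and an explicit statement at baseline. The primary model fails only on the condition that the no-access statement governs and centre means alone reach the analysts.

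The effect on power is modest. Inverse-variance weighting gives about 82% to 83%, in line with the 82.0% for the patient-level model, and an unweighted comparison gives about 77% to 81%. These ranges rest on assumed gamma or lognormal cluster sizes. The larger risk is to prespecification, because the primary analysis and its weights could be settled after the 2022 data are seen.

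**What to change.** Before the 2022 data are extracted, reconcile the Patient data paragraph, HbA1c at 6 months, Other clinical and process of care outcomes, Data management {19} and Statistical methods {20a}. Choose one of two routes.

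1. **Patient records.** State that the ANDA data manager releases coded patient-level 2021 and 2022 records for participating centres to the blinded analysis team, who fit the {20a} model. Limit the no-access statement to the investigators it is meant for.
2. **Centre summaries.** If ANDA governance rules that out, replace the model with a prespecified centre-level regression weighted by 1/(between-centre variance + SD²/n). Extract n and SD per centre as well as the mean, at both audits, and restate the power for that analysis. For an untransformed outcome with no patient-level covariates, n, mean and SD per centre carry the information the random-intercept model uses, so little is lost.

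The cost is a few sentences of protocol wording and a data release within the existing ANDA team. No new data collection is needed.
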